#### 2.1.3 The intervention: rationale for the nitrate preparation, dose, and frequency of administration

Although several other forms of nitrates (e.g. transdermal patch, sublingual sprays) are available, we chose to study NTG ointment (15 mg/day) and oral ISMO (20 mg/day) because these are the only agents for which data on the safety and tolerability in healthy postmenopausal women exist. Moreover, the only studies that have reported changes in bone turnover markers have used either NTG ointment or ISMO. We will study the 20 mg dose of ISMO as our earlier work found that this dose was associated with the greatest change in bone turnover markers [30,31]. There was no difference in headache incidence among women randomized to 5 mg compared to 20 mg. The 20 mg dose is marketed and readily available; this will be important if we use ISMO in a RCT of nitrates for fracture prevention.

We will study the 15 mg/day dose of NTG ointment. This dose was used in the open label trial of NTG for the prevention of oophorectomy induced bone loss [42]. The 15 mg/day dose was based on dose response studies in rodents: a dose of 0.2 mg/kg/day of NTG was associated with the greatest change in bone turnover markers [25,29,58].

We considered using the NTG patch instead of NTG ointment. The NTG patch has a major disadvantage: it has a long (24 hour) average duration of action and, therefore, may cause tachyphylaxis to the bone effects of nitrate. In contrast, the ointment has a much shorter (6 hour) average duration of action so that once daily administration avoids development of tachyphylaxis. We recognize that ointment is more difficult to apply than a transdermal patch and might stain clothing. However, we have used the ointment in 18 women in our pilot study with no mention by women of messiness or staining of clothes.

We will administer both NTG and ISMO once a day i.e. intermittently. While other dosing frequencies may increase BMD (e.g. continuous dosing, or even once weekly dosing), data from both the cardiovascular literature and our observational study suggest that too frequent dosing (e.g. ISMO 20 mg twice a day or NTG every eight hours) is associated with tachyphylaxis while pharmacologic studies suggest that too infrequent dosing (e.g. less than once a day) results in increased frequency and severity of headaches. Thus, once daily or intermittent administration of nitrates will give the greatest change in BMD and the fewest headaches.

As noted earlier above only one other study (funded by NIAMS) is examining the effects of intermittent nitrates on bone in vivo. Our study differs from the NIAMS study in several important ways: 1. We will determine which of NTG or ISMO is better tolerated in healthy postmenopausal women. This has never been done and is vital, both for the success of our proposal and for the potential clinical use of nitrates in future RCT's and clinical practice. 2. We will determine changes in bone turnover markers in response to nitrates, and 3. We will evaluate changes in bone microarchitecture using pQCT. These latter two outcomes are not being assessed in the NIAMS study, yet turnover markers and microarchitecture contribute substantially to fracture risk [9,62,69].

### 2.2 Trial interventions

#### Pilot study

Subjects will receive NTG ointment; at 15 mg/day (one inch of 2% ointment applied to the upper arm) for one week and ISMO at 20 mg/day for one week. The order of treatments will be randomized. In between each treatment there will be a two week washout. The washout exceeds ten half lives of NTG (one hour) and ISMO (five hours) and will eliminate any carryover effects [54-57]. Subjects who report headaches during the wash out will be excluded from the second treatment phase and considered as drop outs in our analysis. We have considered drop outs in our sample size calculations. Both treatments will be administered with placebo (tablet or paste, as appropriate). Subjects will receive standard instructions on how to take the tablet (at bed time with a glass of water; as was given in our earlier study) and patch (apply it first thing in the morning; as was given in the earlier study).

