### 2.4 Study outcomes

#### Pilot study

The primary outcome will be mean headache score associated with each of intermittent NTG and ISMO use. Subjects will be given four seven day diaries, with a VAS for each day of both treatment periods and the wash out period. Subjects will rate their headache upon awakening on a daily basis; our previous study demonstrated that subjects randomized to ISMO who developed headaches reported that the headache was most severe upon awakening and gradually subsided over the day [43]. The VAS uses a 100 mm continuous horizontal line with the left pole labeled "no headache" and the right pole labeled "terrible headache"; subjects will be instructed to draw a vertical line intersecting the VAS indicating the severity of their morning headache. We will calculate the mean headache score with intermittent NTG and intermittent ISMO for each subject. Then we will calculate the mean headache score for all subjects when taking ISMO and when taking NTG. The nitrate that gives the lowest mean headache score will be used in our main study. Our earlier work indicates that the nitrate formulation associated with the most severe headaches will result in the greatest number of drop outs [30]. The VAS can detect subtle changes in subjective complaints (i.e. headache), has documented reliability, and has been used in several studies designed to study the effects of NTG ointment on headache in healthy women [56,57].

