### 2.5 Sample size

#### Pilot study

We wish to detect at least 15 units difference in headache score using the VAS between the intermittent NTG and ISMO groups, which is consistent with a modest effect [57]. We assumed a power of 90% and two sided alpha of 0.05, a standard deviation of 27.78 (based on studies using the VAS to report headaches in healthy women), [56,57] and a small correlation of 0.5 among the repeated measurements [77]. Based on these assumptions, the number of subjects needed for comparing (paired) the mean headache scores for two groups is 20 subjects (Table 4A). We will increase this number by 10%, to account for women who develop headaches that continue into the washout period and cannot go on to the second treatment. Note that this is a conservative approach, in our earlier study all women who developed headaches reported that when they stopped the treatment the headache resolved within 24 hours. Based on these assumptions, we will require 22 subjects for our pilot study.

**Table 4A T4:** Formula used for sample size calculation for pilot study.

*n *= (*Z*_1-*α*/2 _+ *Z*_1-*β*_)^2 ^{1 + (*n *- 1)*ρ*}/(*n*Δ^2^), where *n *= 7, *ρ *= 0.2, Δ = , *β *= 0.1.

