### 2.6 Data analysis

Our main analysis will be intention to treat [86]. There will be no subgroup or interim analysis.

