#### Pilot study

We will use a paired t test to examine for differences in headache score when subjects are randomized to intermittent ISMO compared to the same subjects randomized to intermittent NTG.

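### The pilot's washout exclusion depends on headache, the outcome itself, and the paired t test then loses those women's first-period scores

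*Protocol article*

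**What the plan says.** The pilot is a two-period crossover in 22 women, with one week on each nitrate and a two-week washout between (Protocol article, 2.1).

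- **Exclusion rule (2.2, Pilot study).** "Subjects who report headaches during the wash out will be excluded from the second treatment phase and considered as drop outs in our analysis". No limit is set by day, severity or cause.
- **Drop-out allowance (2.5, Pilot study).** "We will increase this number by 10%, to account for women who develop headaches that continue into the washout period". The allowance is called conservative because "in our earlier study all women who developed headaches reported that when they stopped the treatment the headache resolved within 24 hours". Section 2.1.2 gives the same 24-hour figure.
- **Outcome (2.4, Pilot study).** The outcome is a daily headache rating on awakening, "with a VAS for each day of both treatment periods and the wash out period". The nitrate with the lower mean score over all subjects goes forward to the main study.
- **Analysis (2.6).** "Our main analysis will be intention to treat", and for the pilot, "We will use a paired t test to examine for differences in headache score".

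**The concern.** Sections 2.2 and 2.5 give two triggers for one exclusion. Read literally, section 2.2 removes a woman for a headache on any of the 14 washout days. Section 2.5 counts only a headache that began on treatment and persisted. The 24-hour resolution figure fits the narrower description more easily.

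The statistical problem exists under either wording. Exclusion is triggered by headache, which is what the pilot measures. A paired t test needs both periods, so an excluded woman contributes nothing, although her first week was fully observed. If one drug causes more headache, more women leave from the sequence that starts with it, and those who leave are women who had headache on it. The 10% allowance can replace numbers but cannot undo this selection. The test result is also not an intention-to-treat comparison.

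At stake are the size and precision of the tolerability difference, which section 2.1.3 regards as important for later trials and for practice.

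**Working it through.** **1. The plan's own figures.** Section 2.5: "We wish to detect at least 15 units difference in headache score using the VAS"; "We assumed a power of 90% and two sided alpha of 0.05, a standard deviation of 27.78". The standardised difference is 15/27.78 = 0.540. Table 4A's formula with 7 daily ratings and the text's correlation of 0.5 gives 10.507 × (1 + 6 × 0.5)/(7 × 0.540²) = 20.6, close to the stated 20. Then 20 × 1.10 = 22, so the allowance covers 2 women. (Table 4A prints a correlation of 0.2, which gives 11.3. That is a separate discrepancy.)

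**2. Does the allowance suffice?** The exclusion rate is not given. If it were 10%, 15% or 20% (assumed), the binomial chance of 3 or more exclusions among 22 would be 38%, 66% or 85%.

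**3. Bias of the complete-pair difference.** From the documents: 57% headache on ISMO in the earlier trial (1.4; 5 mg and 20 mg combined, over 12 weeks). Assumed: the NTG headache rate, the mean score *m* of a woman with headache (0 without), 11 women per sequence, and *k*, the share of women with a first-period headache who are then excluded. Exclusion is taken as unrelated to severity.

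The kept fractions are 1 − *k*·pI (ISMO first) and 1 − *k*·pN (NTG first). Summing the ISMO-minus-NTG differences of the women kept, for one woman per sequence, gives *m*(pI − pN)(2 − *k*); the terms for headache on both drugs cancel. Hence

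complete-pair difference = true difference × (2 − *k*)/(2 − *k*(pI + pN)).

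This shrinks the difference whenever the two headache rates sum to less than 100%, and it never reverses the sign.

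Example (57% and 20%, *m* = 40 mm): the true difference is 40 × 0.37 = 14.8 mm. At *k* = 0.5 it becomes 14.8 × 1.5/(2 − 0.385) = 13.7. At *k* = 1 it becomes 14.8/(2 − 0.77) = 12.0.

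| Rates, *m* | True | *k* = 0.25 | *k* = 0.5 | *k* = 1 |
|---|---|---|---|---|
| 57% / 20%, 40 mm | 14.8 | 14.3 | 13.7 | 12.0 |
| 57% / 27%, 50 mm | 15.0 | 14.7 | 14.2 | 12.9 |
| 57% / 4%, 50 mm | 26.5 | 25.1 | 23.4 | 19.1 |
| 57% / 40%, 50 mm | 8.5 | 8.5 | 8.4 | 8.3 |

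Simulated 22-woman trials (severity about 50 mm, SD 20) agree: 14.6, 14.3 and 13.1 for the second row. With equal rates there is no bias.

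**4. One-sided extreme.** If only ISMO-first women are excluded, the difference is *m*{pI(2 − *k*)/(2 − *k*·pI) − pN}. With 57%, 20% and 40 mm this gives 13.5, 11.9 and 7.9 mm for *k* = 0.25, 0.5 and 1, if headaches on the two drugs are independent within a woman.

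**5. Numbers and power.** Complete pairs number 22 − 11*k*(pI + pN). For the first row that is 19.9, 17.8 and 13.5. Simulated power falls between *k* = 0 and *k* = 1 from 43% to 22% (57%/27%) and from 97% to 77% (57%/4%).

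**6. Keeping the scores.** In the same simulations, simple means of all available scores, first-period scores of excluded women included, returned the true difference.

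**The case against.** Four counter-arguments deserve weight.

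- **The t test does not choose the nitrate.** Section 2.4 uses the lower mean over all subjects, and on that wording first-period scores can stay in. This stands for the choice. It does not rescue the test or the estimated difference, and section 2.2 still counts these women as drop-outs in the analysis.
- **The selection need not fall on ISMO alone.** It is tempting to argue that a bedtime ISMO tablet produces a headache recorded on the first washout morning, whereas the ointment is applied in the morning and acts for about 6 hours (2.1.3). That depends on whether the last tablet's morning rating belongs to treatment day 7 or washout day 1, which the article does not say. The one-sided figures in step 4 are therefore an extreme.
- **High exclusion shares are doubtful.** The 57% is a 12-week figure, not a rate after the seventh dose. In the earlier trial, ISMO women who left because of headache did so within two days of randomization, and headaches resolved within 24 hours of stopping (2.1.2). The article therefore does not show that the worst-affected women are the ones lost in washout. A *k* near 1 is an upper bound.
- **A cautious exclusion is compatible with expecting quick resolution.** That is fair. The discrepancy is one of scope between 2.2 and 2.5, and no more is claimed.

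**Conclusion.** The point holds as a flaw of analysis and wording. The rule makes inclusion in the paired t test depend on the outcome, discards observed first-period data, and is stated with two different scopes. With a true difference near 15 mm, the bias is about 0.5 to 3 mm toward no difference if the rule acts equally in both sequences. It is about 7 mm only if every ISMO-first woman with headache and no NTG-first woman is excluded. For a larger true difference of 26.5 mm, total exclusion in both sequences also costs about 7 mm. These sizes rest on the assumed NTG rate, severity and exclusion share, none of which the article gives.

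Stronger conclusions that a reader might draw are not supported:

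- *The wrong nitrate may have been chosen.* Where ISMO is worse and the rates sum to less than 100%, the bias works against NTG. Section 3.0 nevertheless reports significantly less headache on NTG.
- *The 10% allowance must fall short.* That depends on an unknown exclusion rate. At *k* = 0.25 the expected number of complete pairs is 19.9, essentially the 20 required.
- *The 18 women who used the ointment (2.1.3), against 22 planned, show the loss.* The article gives no reason for that number.

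**What to change.** 1. Reconcile the exclusion wording in 2.2 with that in 2.5, and both with the 24-hour resolution figure in 2.1.2 and 2.5. Which headaches should bar a second treatment is a clinical decision for the investigators, and this review does not propose one.
2. Replace the complete-pair t test with an analysis that keeps every randomised woman's available scores, for example a linear mixed model with treatment and period as fixed effects and woman as a random effect. This also brings the pilot closer to the stated intention-to-treat principle.
3. As the pilot is complete, re-run the comparison on the existing diaries, and report the number excluded in washout by sequence.

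The cost is a short re-analysis of at most 22 diaries and a wording change, with no new data. The mixed model relies on missing at random: given the scores observed, exclusion must be unrelated to the unseen second-period score. The counts by sequence help a reader judge how much rests on that.

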## 2.0 Methods

### 2.1 Study design

This research proposal consists of two placebo controlled trials: a four week pilot study and a 27 month main study. The main study will be preceded by a one week nitrate run-in phase. Both the pilot and main study will recruit healthy postmenopausal women, 50 years of age and older, with lumbar spine BMD T scores between 0 and -2.0. The aim of the pilot study is to determine the best tolerated preparation of nitrate for future studies. We will assess eligibility for the pilot study by questionnaire, focused physical examination, electrocardiogram (ECG) and review of most recent BMD measurements. Subjects (n = 22) will be randomly assigned to intermittent NTG at 15 mg/day and intermittent ISMO at 20 mg/day, each for one week. The order of the treatments will be random, accompanied by a placebo control (identical in sight and smell to the active treatment). In between each treatment there will be a two week washout period. Subjects will record the severity of headaches upon awakening every day for four weeks using a visual analog scale (VAS). We will calculate the mean headache score for each subject over both seven day treatment periods and then the mean headache score considering all subjects for each of the NTG and ISMO treatment periods.

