#### 2.1.2 The pilot study and nitrate run-in phase

No published studies compare nitrate preparations with respect to the frequency and severity of headaches. In our earlier study, 16 of the 96 (17%) women randomized to ISMO dropped out due to headaches compared with 2 of 48 (4%) women in the placebo [30,31]. All the women in the ISMO group who dropped out due to headaches did so within two days of randomization. The severity of the headaches determined drop out such that a woman with one day of severe headache was five times more likely to drop out than a woman with mild headaches for several days. Headaches were most severe upon awakening and subsided over the day. All headaches resolved within 24 hours of discontinuing the treatment assignment.

In the open label trial discussed earlier women were given 15 mg/day of NTG ointment and no headaches were reported [42]. Although cross-trial comparisons are problematic, this difference suggests that NTG ointment is better tolerated than oral ISMO. One explanation relates to differences in pharmacokinetics; compared with NTG ointment, ISMO results in a much longer exposure to NO [54-57]. Alternative explanations relate to differences in subjects (the open label trial studied young women with surgical menopause who had hot flashes, while we studied healthy older postmenopausal women), or in ascertainment of adverse events (the open label trial relied on self-report whereas we regularly inquired about headaches). Because there is considerable uncertainty about the relationship of nitrate preparation and headaches, our pilot study will focus on which of NTG or ISMO gives the least headaches.

To minimize differential drop out the main trial will be preceded by a one week nitrate run-in phase. All women eligible and willing to enter the trial will be instructed to take the nitrate, identified in the pilot as the best tolerated, for one week (as noted above women who develop headaches do so within 48 hours of taking the drug). Women who do not develop headaches will enter the main trial and, after 3 months of calcium and vitamin D (pre-treatment phase), will be randomized to placebo or treatment.

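### The pilot rates headache only on awakening, with the tablet taken at bedtime and the topical nitrate applied in the morning, so the rule that selects the main-study nitrate probably favours the ointment by an unknown amount.

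*Protocol article*

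**What the plan says.** Section 2.1 fixes the measurement: "Subjects will record the severity of headaches upon awakening every day for four weeks using a visual analog scale (VAS"). Section 2.4 (Pilot study) repeats it, "Subjects will rate their headache upon awakening on a daily basis", and gives the reason: in the earlier study, "subjects randomized to ISMO who developed headaches reported that the headache was most severe upon awakening and gradually subsided over the day". Section 2.2 (Pilot study) gives the instructions for the tablet and the topical product: "at bed time with a glass of water; as was given in our earlier study) and patch (apply it first thing in the morning").

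The score has a decision attached. Section 2.4 states: "The nitrate that gives the lowest mean headache score will be used in our main study". The reason offered there is that "the nitrate formulation associated with the most severe headaches will result in the greatest number of drop outs". Section 2.1.2 adds: "a woman with one day of severe headache was five times more likely to drop out than a woman with mild headaches for several days".

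On pharmacology, section 2.2 states: "The washout exceeds ten half lives of NTG (one hour) and ISMO (five hours"). Section 2.1.3 gives the ointment an average action of 6 hours, and considers and rejects the patch.

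The Abstract (Discussion) and section 3.0 report that the pilot is complete and that headaches were fewer, or significantly lower, on the ointment, without limiting this to the time of rating.

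**The concern.** The rating time was chosen from the experience of one comparator. ISMO users, who took the tablet at bedtime in the earlier study as in this pilot, had their worst headache on awakening. Nothing comparable is offered for an ointment applied in the morning. If an ointment headache begins after application and fades during the day, the diary has no place to record it. ISMO headache is caught near its worst.

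Random order, washout and the double dummy do not remove this. They deal with period effects, carry-over and expectation, whereas the time of the active dose is tied to the product in every subject and both periods.

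At stake is what the pilot can claim. Its stated aim is to find which nitrate leads to fewer headaches. Section 2.1.3 calls the tolerability answer vital for future trials and clinical practice, and section 3.0 counts finding the nitrate with the least severe headaches among the main objectives. By the authors' own account severity drives drop-out. An awakening score is close to the peak for one product and may miss it for the other.

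**Working it through.** **1. Which product the morning instruction covers.** Section 2.2 says patch. The same paragraph names ointment as the pilot's topical treatment and paste as its placebo, and section 2.1.3 rejects the patch. Ointment is the only sensible reading, but it is an inference. This clause is also the only statement of topical dosing time. Its reference to the earlier study does not fit the authors' own earlier trial, which gave oral ISMO or placebo.

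**2. The plan's own timing statement.** Two weeks of washout is 14 × 24 = 336 hours. That is 336 / 5 = 67.2 half-lives of ISMO and 336 / 1 = 336 of nitroglycerin (NTG), so the statement that washout exceeds ten half-lives is correct. It concerns carry-over between periods and not the hour of rating within a day.

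**3. Time from dose to rating.** Inputs: half-lives of 5 h and 1 h (section 2.2) and ointment action of 6 h (section 2.1.3). Assumptions: 7 to 9 hours from bedtime to awakening, and a diary marked at about the time of the next application.

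| | ISMO tablet | NTG ointment |
|---|---|---|
| Active dose | bedtime | first thing in the morning |
| Rating | on awakening | on awakening |
| Hours since dose | 7 to 9 | about 24 |
| Half-lives since dose | 7/5 = 1.4 to 9/5 = 1.8 | 24/1 = 24 |
| Hours past stated action | none stated | 24 − 6 = 18 |

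The 6-hour action is the more generous guide for the ointment, since it is longer than the 1-hour half-life alone would suggest. Even so, the rating comes 18 hours after it ends.

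**4. How much of the contrast is the clock.** Fraction remaining = 0.5^(hours / half-life). At awakening: ISMO 0.5^1.4 = 38% to 0.5^1.8 = 29%; NTG 0.5^24, essentially nil. If both were rated 8 hours after dosing: ISMO 0.5^(8/5) = 33%; NTG 0.5^8 = 0.4%. So some of the contrast is a real difference in exposure that would remain with matched timing. Drug level is also not a headache score. These figures support a direction only.

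**5. Effect on the selection rule.** Let the ointment be truly worse by d mm, and let u mm be the average headache that the awakening rating misses on the ointment beyond what it misses on ISMO. The expected score difference, ISMO minus ointment, is u − d. The rule then favours the ointment in expectation whenever u > d, even though the ointment is worse. At u = 0 there is no bias. The document gives neither u nor d, so I attach no probability to a wrong selection.

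**The case against.** Four points have weight.

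- **One defective clause.** The ointment's dosing time rests on a sentence that names the wrong product. True, but if that sentence is wrong about the time as well, the dosing instruction itself needs correcting.
- **The 24-hour gap is not stated.** Rating on awakening and applying first thing in the morning are almost simultaneous, and their order is not given. This limits precision. Whether the diary is marked just before or just after application, the daytime hours following the dose are still not rated.
- **Headache may persist, and ISMO may really be worse.** Section 2.1.2 says headaches in the earlier trial resolved within 24 hours of stopping, so some ointment headache could last until the next morning. It also says that ISMO gives much longer nitric oxide exposure, and that the open-label ointment trial reported no headaches, while cautioning against cross-trial comparison. All of this stands. It bounds the certainty and size of the bias without making the rating cover both dosing intervals.
- **The consequence is limited.** The pilot is finished, the bone effect is regarded as a class effect, and the one-week run-in tests the chosen nitrate's tolerability directly before randomisation. A poor choice would mainly cost recruitment. This stands and lowers the severity.

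A reader might go further and infer that the ointment was the wrong choice, pointing to headache drop-out of 19/77 (24.7%) in the ointment run-in (section 3.0) against 16/96 (16.7%) on ISMO in the earlier trial (section 2.1.2). The documents do not support that. The comparison is across studies, Fisher's exact p is 0.25, and run-in failure is defined in section 2.1 as discontinuing because of headache but in sections 2.1.2 and 2.2 as developing one.

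**Conclusion.** The concern holds as a probable bias, not a demonstrated one. The awakening score is taken near ISMO's known headache peak and near the end of the ointment's dosing interval, so the selection rule probably favours the ointment by an amount the document does not allow to be computed. This rests on reading patch as ointment, on an ordinary night's sleep, and on at least some ointment headaches clearing on the day of application.

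As measured, the pilot supports less headache on awakening. It does not establish better overall tolerability, nor does it show that ISMO would have been the better choice. The nitrate-versus-placebo comparison of BMD in the main study is unaffected. Severity is minor to moderate.

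**What to change.** - **Outcome definition (sections 2.1 and 2.4), for any further comparison of nitrates:** define the daily score as the worst headache in the previous 24 hours, rated once a day in both periods. This covers the whole dosing interval of both products, needs no change to dosing times and does not unblind. It is preferable to rating at an equal time after each dose, because the two products act over different lengths of time. Cost: one reworded diary question and some recall error.
- **Completed pilot (Abstract, Discussion, and section 3.0):** state the finding as less headache on awakening, and report headache discontinuations by treatment period beside it. Cost: two sentences and a small table. The claim becomes weaker.
- **Section 2.2:** replace patch with ointment, and confirm the time at which the ointment was applied.

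No change to the run-in or the main trial is needed on this account.
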